### 7.3 Visit 2- Enrollment (V2)

The following procedures will occur at the Enrollment visit (V2). During the enrollment visit the participant will be given instructions on using and begin taking the study medication.

**Table 4: Enrollment (V2)**

| Enrollment Visit- Visit 2 (V2) |                                                                                                                                                                                                                                                                                                           |
|---------------------------------------|-----------------------------------------------------------------------------------------------------------------------------------------------------------------------------------------------------------------------------------------------------------------------------------------------------------|
| Component                      | Procedures                                                                                                                                                                                                                                                                                         |
| Administrative and Regulatory  | 
 
• Confirm eligibility
 
• Review/update locator information
 
• Visit Questionnaire
 
• Provide reimbursement for study visit
 
• Schedule next visit
 
                                                                       |
| Behavioral                     | 
 
• Conduct in depth interview
 
• Provide counseling 
 
– Protocol adherence
 
– Study medication use/adherence
 
 
 
                                                                            |
| Clinical                       | 
 
• Review/update medical history
 
• Review/update concomitant medications
 
• Document pre-existing conditions
 
• Perform full physical examination
 
• Assess fetal heart tones
 
• Provide Screening test results
 
 |
| Medications                    | 
 
• Participants will receive study medication (supply enough for next visit plus 3 extra doses)
 
• Participants will receive instructions for use daily and for PK visits
 
• Participants will receive medication adherence log
 
          |
| Laboratory                     | 
 
• HCV RNA viral load
 
                                                                                                                                                                                                                                    |

### 7.4 Follow-up Visits

#### 7.4.1 Visits 3-5 (PK 1, PK2, PK3)

The following procedures will occur on at the following gestational ages:

- 1) **PK1:** between 25 + 0 and 26 + 6 weeks' gestation (after at least 10 days of therapy)
- 2) **PK2:** 29 + 0 and 30 + 6 weeks' gestation
- 3) **PK3:** 33 + 0 and 34 + 6 weeks' gestation

The PK visits will be scheduled as **early** as possible within the gestational age window to allow for visits that require rescheduling.

**Table 5: Follow-up Visits (PK1, PK2, and PK3)**

| Follow-up Visits 3-5 (PK1, PK2, PK3) |                                                                                                                                                                                                                                                                                                                                                                                                                                                                                                                                                                                                                                                                            |
|--------------------------------------|----------------------------------------------------------------------------------------------------------------------------------------------------------------------------------------------------------------------------------------------------------------------------------------------------------------------------------------------------------------------------------------------------------------------------------------------------------------------------------------------------------------------------------------------------------------------------------------------------------------------------------------------------------------------------|
| Component                            | Procedures                                                                                                                                                                                                                                                                                                                                                                                                                                                                                                                                                                                                                                                                 |
| Administrative and Regulatory | 
 
Review/update locator information
 
Visit questionnaire
 
Provide reimbursement for study visit
 
Record/update AEs
 
Schedule next visit (PK 2, PK 3, End of Treatment)
 
                                                                                                                                                                                                                                                                                                                                                                                                                     |
| Behavioral                    | 
 
Adherence assessment
 
Provide modified counseling 
 
Protocol adherence
 
Instructing participants to contact study staff when in labor/being admitted to labor and delivery
 
Study medication use/adherence
 
 
 
                                                                                                                                                                                                                                                                                                                                      |
| Clinical                      | 
 
Review/update medical history
 
Review/update concomitant medications
 
Perform modified physical examination
 
Assess fetal heart tones
 
Provide available test results (if applicable)
 
Administer timed dose of study medication
 
Provide study medication with sufficient supply until next visit (PK1 and PK2) or until completion of treatment course (PK3) with 3 additional doses
 
Adherence assessment
 
                                                                                                                                                     |
| Laboratory                    | 
 
Collect blood 
 
Intensive PK sampling (all visits)
 
Protein binding assay (all visits)
 
 
 
PRIOR TO VISIT DOSING: 
 
CBC with differential and platelets (PK1 and PK2)
 
Hepatic function panel (AST, ALT, albumin, total and direct bilirubin, alkaline phosphatase) (PK1 and PK2)
 
PT/INR (PK1 and PK2)
 
Creatinine (PK1 and PK2)
 
Lipase (PK1 and PK2)
 
Creatine kinase (PK1 and PK2)
 
HCV RNA viral load (PK1 and PK2)
 
HCV Resistance Testing*
 
 
 
 |

\*as indicated per protocol section 9.3

### LDV and SOF PK Evaluation

Participants will be instructed not to take their daily dose at home but rather to bring their dose of SOF/LDV FDC to their visit for a timed administration. Alternately, a dose will be dispensed by the PoR for the PK visits. Participants will be instructed

about dietary restrictions for these visits as outlined in section 7.6. Participants will have their first PK plasma drawn before the time of their dose of SOF/LDV FDC. The dose at each PK visit will be timed and blood samples will be collected at each PK visit as follows (relative to the timed dose): pre-dose, 0.5, 1, 2, 3, 4, 5, 8 and 12 hours. An intravenous catheter will be placed prior to the pre-dose draw and will be in place throughout the PK visits. A saline solution will be used at a slow drip to attempt to keep the vein patent. In the event that the catheter fails, participants may have another IV inserted or individual venipuncture(s) to attempt to collect all PK samples. If a PK sample(s) cannot be obtained, then the participant will remain evaluable, if at least one sample is obtained at each PK visit. For further details, see section 7.6 Pharmacokinetics.

#### 7.4.2 End of Treatment Visit (V6)

The following procedures will occur at the End of Treatment visit. This visit will be scheduled within 7 days of completion of the 12 week course of study medication. The purpose of this visit will be to collect any remaining study medication and to collect and follow up on any adverse events. Participants will also be reminded to call the research staff when they present to the hospital for delivery.

**Table 6: End of Treatment Visit**

| End of Treatment Visit        |                                                                                                                                                                                                                                                                                      |
|-------------------------------|--------------------------------------------------------------------------------------------------------------------------------------------------------------------------------------------------------------------------------------------------------------------------------------|
| Component                     | Procedures                                                                                                                                                                                                                                                                           |
| Administrative and Regulatory | 
 
Review/update locator information
 
Visit Questionnaire
 
Provide reimbursement
 
Record/update AEs
 
                                                                                                           |
| Behavioral                    | 
 
Protocol adherence counseling, including delivery visit instructions
 
Collect remaining study medication
 
Collect medication administration log
 
Conduct in depth interview
 
                                |
| Clinical                      | 
 
Review/update medical history
 
Review/update concomitant medications
 
Perform modified physical examination
 
Provide available test results if available
 
Assess fetal heart tones (if applicable)
 
 |
| Laboratory                    | 
 
HCV RNA viral load
 
HCV resistance testing*
 
                                                                                                                                                                                |

\*as clinically indicated

#### 7.4.3 Delivery Visit (in person visit or chart review)

Participants will be instructed to contact the study staff when they are in labor/admitted to labor and delivery, regardless of delivery location. The Delivery Visit will occur during admission for participants delivering at Magee-Womens Hospital and will include maternal and cord blood samples. The date of the Delivery Visit for participants who deliver at Magee will be the date the study staff makes the first contact with the participant during her delivery admission, regardless if procedures occur over more than one day. Participants who deliver at an outside location will be contacted by phone as close to delivery as possible to complete the applicable Delivery Visit study procedures (i.e. questionnaire, update locator

information, update medical history). The Delivery Visit date for these participants will be the date of the completed phone call. All participants, regardless of delivery location will undergo a chart review to obtain delivery outcomes/variables. A copy of the delivery records will be placed in the participant's research chart. In the event that the participant delivers prematurely at Magee-Womens Hospital of UPMC and is still taking study medication, then procedures from previously scheduled visits (V2-V6) may be performed, excluding intensive PK sampling. Rather than intensive PK sampling, a single maternal blood sample will be taken as close to the time of delivery as possible and cord blood will be collected for LDV/SOF PK analysis and the protein binding assay.

**Table 7: Delivery Visit**

| Delivery Visit                              |                                                                                                                                                                                                                                                                                                                                                                                                                                                                                                                                                                                                                                  |
|----------------------------------------------------|----------------------------------------------------------------------------------------------------------------------------------------------------------------------------------------------------------------------------------------------------------------------------------------------------------------------------------------------------------------------------------------------------------------------------------------------------------------------------------------------------------------------------------------------------------------------------------------------------------------------------------|
| Component                                   | Procedures                                                                                                                                                                                                                                                                                                                                                                                                                                                                                                                                                                                                                |
| Administrative and Regulatory               | 
 
• Review/update locator information
 
• Visit Questionnaire
 
• Provide reimbursement, as applicable
 
• Record/update AEs
 
• Schedule next visit
 
                                                                                                                                                                                                                                                                                                                                                                                                 |
| Behavioral                                  | 
 
• Protocol adherence counseling
 
• Study medication use/adherence (if still on study medication)
 
                                                                                                                                                                                                                                                                                                                                                                                                                                                                       |
| Clinical                                    | 
 
• Review/update medical history
 
• Review/update concomitant medications
 
• Provide available test results if available
 
• Perform modified physical examination (or obtain from medical record)
 
• Dispense study medication to complete 12 week course (if still on study medication)*
 
                                                                                                                                                                                                                                                       |
| Medical Record Review for Delivery Outcomes | 
 
• Type of pregnancy outcome
 
• Gestational age at pregnancy outcome
 
• Method of calculation for gestational age at pregnancy outcome
 
• If delivery, type of delivery (e.g., vaginal, vaginal forceps-assisted, vaginal vacuum-assisted, cesarean section)
 
• Complications related to pregnancy outcome 
 
– Delivery complications (e.g., intrapartum and/or postpartum hemorrhage, non-reassuring fetal status, chorioamnionitis)
 
– Other complications not related to a delivery
 
 
 
 |
| Baseline Infant Information**               | 
 
• Sex
 
• Weight
 
• Length
 
• Head circumference
 
• Apgar scores
 
• Medical history (e.g., sepsis, respiratory distress, any abnormalities noted on infant exam)
 
• Medication history
 
                                                                                                                                                                                                                                                                                                                                          |
| Laboratory***                               | 
 
• Maternal HCV RNA viral load
 
• Cord blood collection for HCV RNA viral load
 
• Cord blood collection for PK analysis (if still on study medication)
 
• Maternal plasma sample for PK analysis (if still on study medication)
 
• Maternal protein binding assay (if still on study medication)
 
• Cord blood protein binding assay (if still on study medication)
 
                                                                                                                                                                     |

\*Unless participant intends to breastfeed, in which case study medication will be discontinued

\*\*All Baseline Infant Information may be extracted from the infant medical record as available

\*\*\*Laboratory tests performed as applicable for participants who deliver at Magee-Womens Hospital

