#### **3.2 Secondary Objectives**

1. To determine the rate of SVR12 of hepatitis C virus genotype 1, 4, 5 or 6 with LDV/SOF FDC treatment for 12 weeks during pregnancy.
2. To evaluate the maternal and neonatal safety of hepatitis C treatment with LDV/SOF FDC during pregnancy.

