#### 7.4.5 Infant Follow-Up Visits (iV1, iV2, iV3)

After delivery, infants will be seen at the following time points:

iV1: 8 weeks  $\pm$  6 weeks

iV2: 6 months  $\pm$  2 weeks

iV3: 12 months  $\pm$  2 weeks

The following procedures will occur at the Infant Follow-Up Visits (iV1, iV2, iV3). If blood sampling is not possible, then the results can be collected from the infant's medical record if available. Results of physical and developmental exams

will be shared with the mother, and if necessary with the infant's routine healthcare provider.

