**Table 8: Infant Follow-Up Visits (iV1, iV2, iV3)**

| Visit iV1, iV2, iV3 Infant Follow-Up Visits |                                                                                                                                                                                                                                                                                                                                                                              |
|---------------------------------------------|------------------------------------------------------------------------------------------------------------------------------------------------------------------------------------------------------------------------------------------------------------------------------------------------------------------------------------------------------------------------------|
| Component                                   | Procedures                                                                                                                                                                                                                                                                                                                                                                   |
| Administrative and Regulatory        | 
 
• Review/update locator information
 
• Review infant demographics (iV1)
 
• Sign release(s) for medical records for infant
 
• Provide reimbursement
 
• Schedule next visit (iV1, iV2)
 
                                                                                                       |
| Clinical                             | 
 
• Review/update medical history
 
• Review/update concomitant medications
 
• Growth assessment including weight, length, and head circumference
 
• Perform age appropriate physical examination
 
• Bayley's Developmental Exam (iV2 and iV3 only)
 
• Provide available test results
 
 |

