### **8.3 Adverse Events Definitions and Reporting Requirements**

#### **8.3.1 Adverse Events**

An AE is defined as any untoward medical occurrence in a clinical research participant administered an investigational medication and which does not necessarily have a causal relationship with the investigational medication. As such, an AE can be an unfavorable or unintended sign (including an abnormal laboratory finding, for example), symptom or disease temporally associated with the use of an investigational medication, whether or not considered related to the medication. The term “investigational medication” for this study refers to the study medication.

Study participants will be provided instructions for contacting the study site to report any untoward medical occurrences they may experience throughout their participation in the study. Participants receiving prenatal care and/or delivering at Magee-Womens Hospital will be instructed to come to Magee-Womens Hospital if they experience any adverse events requiring evaluation. Participants will be seen by a physician investigator/study clinician. If the participant is not receiving care at Magee-Womens Hospital, then they will be instructed to seek medical care with their local primary care physician/obstetrical team. Close communication with the participant and the primary care provider/obstetrical team will be maintained. Participants may have an unscheduled visit with the physician investigator/study clinicians as necessary or desired. In cases of potentially life-threatening events, participants will be instructed to seek immediate emergency care. With appropriate permission of the participant, whenever possible, records from all non-study medical providers related to untoward medical occurrences will be obtained and required data elements will be abstracted and recorded on study CRFs. All participants reporting an untoward medical occurrence will be followed clinically until the occurrence resolves (returns to baseline) or stabilizes.

Study site staff will document all AEs reported by or observed in enrolled study participants regardless of severity and presumed relationship to investigational medication, including gradable laboratory findings. AE severity will be graded per the DAIDS Table for Grading Adult and Pediatric Adverse Events, Version 1.0, December 2004 (Clarification dated August 2009).

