## APPENDIX II: SCHEDULE OF STUDY VISITS AND EVALUATIONS (Infant)

|                                      | Delivery*** | iV1
(Month 1-3) | iV2
(Month 6) | iV3
(Month 12) |
|--------------------------------------|-------------|--------------------|------------------|-------------------|
| ADMINISTRATIVE AND REGULATORY |             |                    |                  |                   |
| Assignment of PTID                   | X           |                    |                  |                   |
| Locator information                  | X           | X                  | X                | X                 |
| Demographic information              | X           |                    |                  |                   |
| Reimbursement                        | X           | X                  | X                | X                 |
| Record/update AEs                    |             | X                  | X                | X                 |
| Schedule next visit                  | X           | X                  | X                |                   |
| CLINICAL                      |             |                    |                  |                   |
| Medical history **                   | X           | X                  | X                | X                 |
| Concomitant medications**            | X           | X                  | X                | X                 |
| Document pre-existing conditions**   | X           | X                  |                  |                   |
| Physical examination **              | X           | X                  | X                | X                 |
| Collect growth parameters **         | X           | X                  | X                | X                 |
| Collect Baseline Information**       | X           |                    |                  |                   |
| Provide available test results       |             | X                  | X                | X                 |
| Neurodevelopmental Exam              |             |                    | X                | X                 |
| LABORATORY                    |             |                    |                  |                   |
| HCV RNA viral load                   | X           | X                  | X                | X*                |
| HCV Resistance testing               | *           | *                  | *                | *                 |

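### The protocol contradicts itself on infant AE recording around birth, so non-structural illness in an exposed newborn can be kept as history and bypass AE grading and reporting

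*Protocol*

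**What the plan says.** Section 3.2 includes neonatal safety among the secondary objectives: "To evaluate the maternal and neonatal safety of hepatitis C treatment with LDV/SOF FDC during pregnancy". Section 10.2 enrols infants upon delivery. Section 8.3.1 states the general duty: "Study site staff will document all AEs reported by or observed in enrolled study participants regardless of severity". Section 4.5 adds that infant AEs unresolved at iV3 are followed until they resolve.

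The visit tables and the infant schedule say something else:

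- Table 7 (Delivery Visit) has a Baseline Infant Information block, which includes "Medical history (e.g., sepsis, respiratory distress, any abnormalities noted on infant exam".
- Appendix II (Infant) leaves the row "Record/update AEs" empty at Delivery and marks it at iV1, iV2 and iV3. It marks "Document pre-existing conditions" at Delivery and again at iV1.
- Table 8, the procedure list for the infant visits, has "Review/update medical history" but no AE item at any visit.
- Section 8.3.1 defines an AE as "any untoward medical occurrence in a clinical research participant administered an investigational medication". It does not mention a fetus or infant exposed through the mother.

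**The concern.** For the mother, baseline comes before the drug, so separating pre-existing conditions from AEs makes sense. For the infant the order is reversed. The planned exposure is in utero, so anything found at birth comes after it. Calling such a finding baseline or pre-existing treats a possible outcome as a starting condition.

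The label matters because several safety steps attach to AEs. These are severity grading (Section 8.3.1), relatedness (8.3.3), monthly AE reporting to the manufacturer and SAE reporting to the IRB and FDA (8.4.1). Section 8.3.2 defines an SAE as a kind of AE, so an illness never entered as an AE may not be tested against the SAE criteria. Section 8.2 bases a recommendation to pause or stop on the type and frequency of AEs, and Section 10.5.4 plans no DSMB. Section 2.5 reports no experience with the drug in pregnant women, and Section 13.3.1 says its effects on the fetus are unknown. Section 2.1 cites assisted ventilation, intensive care and neonatal seizure as associated with maternal HCV, so illness around birth is foreseeable in this population.

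**Working it through.** The protocol gives no figure to reproduce. The check sets the passages side by side, with two small calculations.

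**When exposure ends.** Treatment starts at 23+0 to 24+6 weeks and lasts 12 weeks (Protocol Summary). 23+0 plus 12 weeks is 35+0; 24+6 plus 12 weeks is 36+6. A mother who completes treatment before delivering has therefore stopped by about 35+0 to 36+6. If she delivers while still on drug and intends to breastfeed, the drug is stopped (Table 7 footnote, Section 9.3). In both cases the infant's planned exposure lies before birth.

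**When scheduled infant AE recording starts.** Section 7.4.5 sets iV1 at 8 weeks plus or minus 6 weeks: 8 − 6 = 2 weeks and 8 + 6 = 14 weeks. The first visit at which Appendix II marks infant AE recording is thus at a target age of 2 to 14 weeks. Appendix II heads the same visit Month 1-3.

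**The passages compared.**

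| Place | Infant AE recording |
|---|---|
| Section 10.2 with 8.3.1 | Infants enrolled at delivery; all AEs in enrolled participants documented, so from birth |
| Section 4.5 | Infant AEs expected and followed past iV3 if unresolved |
| Table 7 (Delivery Visit) | AE item listed without saying mother or infant; neonatal illness listed as baseline history |
| Appendix I | AE row marked at Delivery for the mother |
| Appendix II | AE row blank at Delivery for the infant, marked at iV1 to iV3 (3 of 4 columns) |
| Table 8 | No AE item at iV1, iV2 or iV3 (0 of 3 visits) |
| Section 8.3.1 definition | Tied to a participant administered the drug |
| Section 13.6.2 | For births outside the study hospital, infant procedures begin at iV1 |

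**What follows.** Table 7 alone could be read as covering the infant. But Appendices I and II are where mother and infant are scheduled separately, and there the Delivery AE row is marked for the mother and not for the infant. At iV1 both the AE row and the pre-existing-conditions row are marked, and no rule says which conditions go in which. A site following Appendix II and Table 8 could store neonatal sepsis or respiratory distress as history and still comply with the schedule. A site following Sections 8.3.1 and 10.2 would enter the same illness as an AE.

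**What is not touched.** The infant endpoints in Section 10.2 are major malformations, growth including birth size, neurodevelopment and perinatal HCV transmission. None is derived from AE records. Adverse events appear only in the maternal endpoint list (Section 10.2.2). A congenital anomaly is named in the SAE definition (Section 8.3.2).

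**The case against.** The strongest reply is that the governing text already requires infant AEs from birth. Infants are participants from delivery, all their AEs are to be documented, grading uses an adult and pediatric table, and Section 4.5 plainly treats infants as AE subjects. This weakens a literal reading of the word administered. The baseline block in Table 7 also holds birth weight, length and head circumference, which are named safety endpoints, so the heading need not mean excluded from safety. AE recording at iV1 is not limited to events starting then and could reach back to birth. The second pre-existing mark at iV1 may exist only for infants born elsewhere. Illness that prolongs the birth admission meets an SAE criterion if it is recognised as an AE.

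Much of this stands. It shows that the protocol probably intends infant AEs to be captured from birth. It does not remove the conflict, because the infant schedule, Table 8 and the AE definition do not carry that intention through.

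A reader might infer more: that birth-period events drop out of the neonatal safety endpoint, or that a neonatal AE rate is biased towards zero. The documents do not support either. The named infant endpoints do not depend on AE records, no infant AE rate is defined as an endpoint, and the illness data are still abstracted from the chart and could be graded later. Nor can one say that such illness is absent from the monthly review: Section 8.2 leaves the content of those reports to be agreed separately.

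**Conclusion.** The point holds as an internal contradiction with a consequence for safety handling. Sections 4.5, 8.3.1 and 10.2 imply infant AE recording from birth. Appendix II, Table 7 (Delivery Visit), Table 8 and the wording of the AE definition do not deliver it. If the schedule is followed as written, non-structural illness between birth and iV1 can be held as history without grading, relatedness assessment or AE/SAE reporting.

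The extent is one blank AE cell at Delivery, three infant visits without an AE item in Table 8, and a target interval of 2 to 14 weeks before the first scheduled infant AE entry. The effect on any estimate cannot be quantified, because the documents give no expected rate of neonatal illness and define no infant AE endpoint. The conclusion assumes that sites work from the visit tables and Appendix II, and that AE recording at iV1 is not otherwise instructed to reach back to birth.

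**What to change.** Reconcile the passages before infants are enrolled:

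- In Appendix II, mark infant AE recording at Delivery.
- Add AE recording to Table 8 at iV1, iV2 and iV3, to match Appendix II.
- State in Table 7 (Delivery Visit), and at iV1 for births elsewhere, that any untoward finding abstracted as infant history since birth is also entered as an infant AE or SAE with grade and relatedness.
- Remove the infant pre-existing-conditions row, or restrict it to conditions documented before the mother's first dose.
- Extend the AE definition in Section 8.3.1 to a fetus or infant exposed in utero.

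The cost is a protocol wording and CRF change. The chart data are already abstracted, so no visit or procedure is added. The downside is more AE and SAE entries to process.
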